#### Target trial emulation using observational data from TriNetX and CPRD

*Eligibility criteria*. Anonymised, person-level, electronic health data will be extracted from TriNetX and CPRD, linked across primary care, ED, inpatients, outpatients, and mortality subsets. The study period will be from 01/01/2014 to 01/01/2024. Included will be men and women aged 16–54 years. The study will take an open cohort design with patients entering the cohort when the following criteria are met:

Either: ≥1 epilepsy disease or symptom code recorded during the study period and two separate valproate prescription instances over the preceding 12 months before at least one of the epilepsy disease or symptom codes;

Or: ≥1 epilepsy disease or symptom code recorded any time before the study period with at least two separate valproate prescription instances over 12 months during the study period.

TriNetX and CPRD use ICD-10-CM and SNOMED codes, respectively. The coding strategy combining disease and symptom codes with valproate, as used our published study successfully [20], was shown to accurately identify epilepsy cases in our prior work [28,29].

Treatment arms:

Withdrawn valproate and commenced lamotrigineWithdrawn valproate and commenced levetiracetamWithdrawn valproate and no new ASM commencedContinues valproate

*Treatment assignment*. Baseline (time 0) will be defined as when valproate dose reduction commences (treatment arms 1–3) or prescription of valproate at a matched time (arm 4). Eligible individuals are assigned at baseline to the treatment strategy that their data are consistent with [21]. To emulate randomisation, adjustment is made for baseline confounders using Robins’ generalised methods (g-methods, e.g., inverse probability weighting) [21], considering age, sex, ethnicity, deprivation, type of epilepsy (using G40 codes), baseline seizure frequency (symptom codes recorded over preceding 12 months), alcohol excess, developmental delay, Cambridge Multimorbidity Score, length of valproate treatment, valproate dose, and ASMs used other than valproate. The final set of covariates required to adjust for confounding will be chosen using a causal directed acyclic graph [21].

*Outcomes*. These are listed in the target trial design section and derived from our prior work [1,20,30,31], and public consultation. All coded events will be recorded for flexible categorical or continuous analyses, as needed.

*Causal estimand*: Assesses impact of treatment arms 1–3 vs. 4 on outcome (per-protocol assumption as observational data limits ITT assessment) [21].

*Start and end of follow-up*. The start of follow-up (Time 0 or index date) will be defined as when valproate treatment discontinued (treatment arms 1–3) or prescription of valproate at a matched time (arm 4). For time-to-first-event analyses, the end of follow-up will be defined as when the outcome occurs, censoring (including deviation from assigned treatment or leaving the study catchment area), or 10 years. For recurrent events analyses, alongside censoring as above, the end of follow-up will be 10 years, allowing for all events to be assessed throughout follow-up.

*Statistical analysis*: mirrors target trial section.

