### Addressing Aim 1: Target trial emulation

#### Target trial design

A hypothetical target trial will be emulated in which young men and women taking valproate would be randomised to either continue valproate, switch to lamotrigine or levetiracetam, or discontinue valproate [21]. The following mortality and morbidity outcomes would be assessed over the subsequent five years:

Deaths (all-cause/epilepsy-related);ED/hospital admissions (all-cause/epilepsy-related);Seizures (symptom codes);Falls;Injuries;Burns;Aspiration pneumonia;Manic/bipolar episodes;New-onset depression;Self-harm/suicide;A composite morbidity index incorporating seizures, injuries, admissions, depression.

Intention-to-treat (ITT) and per-protocol effects would be assessed between groups [21]. Analysis would take a time-to-first-event approach (Cox-proportional hazards model) for deaths, new-onset depression and composite morbidity. A recurrent events approach (e.g., Prentice-Williams-Peterson Total Time Model) would be taken for the remaining outcomes.

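### Patients first coded with epilepsy during the study period and then started on valproate enter only if a further epilepsy or symptom code is recorded, and nothing requires that code to precede time 0

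*Protocol article*

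**What the plan says.** The Eligibility criteria paragraph of the protocol article sets the window ("The study period will be from 01/01/2014 to 01/01/2024") and an "open cohort design with patients entering the cohort when the following criteria are met". There are two alternative ways in.

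- **Route 1:** "≥1 epilepsy disease or symptom code recorded during the study period", together with "two separate valproate prescription instances over the preceding 12 months before at least one of the epilepsy disease or symptom codes".
- **Route 2:** "≥1 epilepsy disease or symptom code recorded any time before the study period", together with "at least two separate valproate prescription instances over 12 months during the study period".

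The Treatment assignment paragraph places time 0 at the start of valproate dose reduction for arms 1–3. The paragraph on start and end of follow-up places it at discontinuation. Both give arm 4 a valproate prescription at a matched time, without naming the matching variable. Treatment assignment also says that eligible people are assigned at baseline. It lists seizure symptom codes over the previous 12 months and length of valproate treatment among the adjustment variables. The outcome list in the Target trial design includes "Seizures (symptom codes" and a composite that contains seizures.

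**The concern.** The usual clinical order is diagnosis, then treatment. Route 1 requires the reverse order for at least one code, and route 2, which accepts the usual order, is closed to anyone first coded after the start of 2014. So the recently diagnosed part of the cohort is filtered on having a code while on or shortly after valproate, and the long-diagnosed part is not. No reason is given for treating the two differently.

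Two things are at stake. The first is absolute risk. Aim 2 produces individual predicted risks, and the Aim 1 figures are meant for the risk section of a national decision support tool. Leaving out patients who do well enough to generate no further code can make those risks too high. The second is the comparison between arms. Symptom codes are at once an entry criterion, a baseline covariate and an outcome. If a code recorded after time 0 can confer eligibility, entry is conditioned on an outcome-type event. The time available to collect that code is then shorter for someone who has stopped valproate than for someone who continues.

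**Working it through.** No figure in the protocol rests on this rule, and the sample sizes in Table 1 do not change. The check has two parts: the logic of the routes, then an illustration of size with no treatment effect.

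**Logic.** Compare two patients who differ only in the date of the first code. Both start valproate after that code, within the study period, and have no later code.

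| First code | Route 1 (code after two prescriptions) | Route 2 (code before 01/01/2014) | Enters? |
|---|---|---|---|
| 2013 | not met | met | yes |
| 2016 | not met | not met | no |

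The 2016 patient enters only with a further disease or symptom code that has two valproate prescriptions in the 12 months before it. After withdrawal, that chance ends at most 12 months after the earlier of the last two prescriptions. For a continuer it stays open to the end of the study period.

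**Assumptions for the illustration (none from the documents).** Newly coded patients; quarterly prescriptions; time 0 uniform between 0.5 and 3 years after the first code; withdrawal independent of risk; 5 years of follow-up; further codes at a constant rate r per year. The second prescription is at 0.25 years, so the window before time 0 is uniform on 0.25 to 2.75 years. For a window uniform on (a, b):

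P(no code) = [exp(−ra) − exp(−rb)] / [r(b − a)]

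**Reading A: the code must precede time 0, and arms are matched on valproate duration.** At r = 0.3, P(no code) = (0.9277 − 0.4382)/0.75 = 0.653, so 35% are admitted in each arm and the null rate ratio is 1.00. To see the enrichment, let r vary between patients (gamma, mean 0.3, squared coefficient of variation 1):

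- P(no code) = ln(1.825/1.075)/0.75 = 0.706, so 29% are admitted.
- Rate carried by those left out: (1/1.075 − 1/1.825)/2.5 = 0.153.
- Mean rate of those admitted: (0.300 − 0.153)/0.294 = 0.50 per year, against 0.30 overall.

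**Reading B: the code may follow time 0.** With the last two prescriptions 0.25 years apart, a withdrawn patient can qualify until 0.75 years after time 0 (window 1 to 3.5 years). A continuer can qualify throughout follow-up (window 5.25 to 7.75 years). At r = 0.3, without variation between patients:

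- Withdrawn: 1 − (0.7408 − 0.3499)/0.75 = 0.479 admitted.
- Continuing: 1 − (0.2070 − 0.0978)/0.75 = 0.854 admitted.
- Anyone with a code in the first 9 months is admitted in either arm, so the spurious 9-month rate ratio is 0.854/0.479 = 1.78.

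The same formula gives 0.199 against 0.477 at r = 0.1 (ratio 2.39). At r = 3 the ratio is 1.01 without variation, and 1.10 in simulation with variation. Over 5 years, simulated rate ratios for r from 0.1 to 3, with and without variation, run from 0.77 to 1.16, so the direction is not fixed.

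**Continuers not matched on valproate duration, code required before time 0.** Take withdrawers 1 year and continuers 3 years after starting, with the second prescription at 0.1 years (windows 0.9 and 2.9), and an equal mix of high and low code rates. Mean rate among those admitted = Σ r(1 − e^(−rw)) / Σ (1 − e^(−rw)), where w is the window:

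| Rates (high, low) | Withdrawn | Continuing | Ratio |
|---|---|---|---|
| 1, 0.2 | 0.826 | 0.746 | 1.11 |
| 1, 0.1 | 0.886 | 0.811 | 1.09 |
| 2, 0.2 | 1.703 | 1.449 | 1.18 |

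With equal windows the ratio is exactly 1. These are crude rates, before any adjustment.

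**The case against.** A reader might infer that the rule by itself selects withdrawn and continuing patients differently and pushes the result against withdrawal. The documents do not support that. Patients enter when the criteria are met and are assigned at baseline as eligible individuals, which suggests that eligibility is complete by time 0. Arm 4 has a matched time 0. If the matching is on valproate duration, both arms face the same condition over the same span and the arm difference is zero. Even where the arms do differ, the direction of the 5-year bias depends on the assumed rates.

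A reader might also infer that the later code always marks disease activity. It need not: a diagnosis re-recorded at a routine visit qualifies, and the data are linked across primary care, outpatients and hospital. A newly diagnosed patient whose first code already follows two prescriptions needs no further one. Adjustment for seizure frequency in the prior 12 months and for treatment length covers part of any selection before baseline.

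Finally, the protocol says that its strategy of combining codes with valproate identified epilepsy accurately in earlier work. A changed rule alters the case definition, and whether that validation depended on the order of code and prescription cannot be seen here.

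All of this limits the claim. It does not explain why the two routes differ, adjustment cannot bring back patients who were never admitted, and no sentence says that the code must precede time 0. Reading the qualifying date against discontinuation also leaves a gap: a code recorded during a taper would precede time 0 and could admit a withdrawn patient, and continuers have no taper.

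**Conclusion.** The point holds in a limited form. Followed as written, the rule excludes patients first coded from 2014 onward who start valproate afterwards and stay code-free, while admitting the same patients if first coded before 2014. Unless routine re-recording of diagnoses is frequent, this enriches the incident part of the cohort for active epilepsy and inflates absolute risks. In one illustration the admitted mean rate is 0.50 against 0.30 per year.

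Unequal selection by arm is conditional. It needs either a qualifying code after time 0, which the text does not exclude, or continuers not matched on time since starting valproate. In those cases the comparison can be biased in either direction. If all criteria are met before a time 0 matched on valproate duration, only the enrichment remains.

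Every size quoted rests on assumed code rates and prescription intervals. The share of the cohort affected is unknown, and none of the figures is diluted by route 2 patients.

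**What to change.** Reconcile the two definitions of time 0 into one, and replace both routes by a single rule evaluated there: at least one epilepsy disease or symptom code on or before time 0, and at least two separate valproate prescriptions in the 12 months up to time 0. State that no code after time 0 confers eligibility, and that the matched time in arm 4 is matched on time since starting valproate. Reconciling time 0 alone would not readmit the code-free patients.

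The cost is a rewritten eligibility sentence, a short addition on matching and a changed query, and data access was still being sought when the protocol was written. Patients now left out for want of a later code become eligible. The downside is a slightly less strict case definition for incident patients, some of whom will have only one code. A sensitivity analysis requiring two codes on or before time 0 would show whether that matters.

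### Arms 1–3 enter at a change in valproate made for any reason and arm 4 at a matched prescription, so early events after withdrawal may be partly reverse-caused

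*Protocol article*

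**What the plan says.** All references are to the protocol article, section on target trial emulation using observational data from TriNetX and CPRD, unless stated.

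- **Time 0, arms 1–3.** Under Treatment assignment: "Baseline (time 0) will be defined as when valproate dose reduction commences". Under Start and end of follow-up: "The start of follow-up (Time 0 or index date) will be defined as when valproate treatment discontinued (treatment arms 1–3". These are two different dates and must be reconciled, but that is a separate matter. Neither carries a condition on why valproate was changed.
- **Time 0, arm 4.** "or prescription of valproate at a matched time (arm 4". The matching is described by time, not by clinical state.
- **Assignment.** "Eligible individuals are assigned at baseline to the treatment strategy that their data are consistent with".
- **Adjustment.** Demographic items, epilepsy type, "baseline seizure frequency (symptom codes recorded over preceding 12 months", and "alcohol excess, developmental delay, Cambridge Multimorbidity Score, length of valproate treatment, valproate dose, and ASMs used other than valproate". The list is provisional: "The final set of covariates required to adjust for confounding will be chosen using a causal directed acyclic graph".
- **Outcomes (Target trial design).** The list opens with "Deaths (all-cause/epilepsy-related);ED/hospital admissions (all-cause/epilepsy-related" and goes on to seizures, injuries, self-harm and a composite that includes seizures and admissions.
- **Eligibility.** Age, epilepsy codes and repeated valproate prescriptions. Neither entry route refers to hospital stay, acute illness or end-of-life care at time 0.

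**The concern.** A drug is sometimes changed because the patient is already deteriorating. Valproate may be stopped during an admission, after an overdose or organ complication, after a cluster of seizures, or because a dying patient no longer takes tablets. If the record then fits arm 1, 2 or 3, the remainder of that illness falls inside follow-up and is attributed to withdrawal. A target trial would not normally randomise someone in that state.

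An event that wholly precedes time 0 is not counted. What can be counted is same-day coding, a stay still open at time 0, a repeat attendance, and death from the same illness.

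The listed covariates do not date such a trigger. Three seizure codes last week and three codes eleven months ago give the same 12-month value, and the Cambridge Multimorbidity Score describes chronic burden.

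The bias from this route would run towards Hypothesis 1, that some harms increase on withdrawal. It would also reach the Aim 2 model, where treatment arm is a forced predictor of a composite containing epilepsy-related death, seizures and admissions. Under Pathways to impact, Aim 1 figures are intended for a national decision support tool.

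**Working it through.** **1. The plan's own figure.** Table 1 uses ED attendance in the pilot: p1 = 2977/8021 = 0.3712 (withdrawn) and p2 = 2471/8021 = 0.3081 (continuing), a difference of 0.0631. With two-sided alpha 0.05 and power 0.80:

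n = (1.960 + 0.842)² × [p1(1−p1) + p2(1−p2)] / (p1−p2)² = 7.849 × (0.2334 + 0.2132) / 0.00398, which rounds up to 881 per group.

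The stated 881 reproduces and is not in dispute. It supplies a scale for what follows.

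**2. ED attendance with no true effect.** Let f be the share of withdrawals triggered by an illness that always leads to a counted ED attendance. The apparent withdrawn risk is p2 + f(1−p2), so the spurious difference is f × 0.6919. The protocol gives no value for f; the range is an assumption.

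| f | Spurious difference (points) | Risk ratio |
|---|---|---|
| 1% | 0.7 | 1.02 |
| 2% | 1.4 | 1.04 |
| 5% | 3.5 | 1.11 |
| 10% | 6.9 | 1.22 |

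The f that would equal the whole pilot difference is 0.0631/(q−0.3081), where q is the ED risk in triggered patients: 9.1% for q = 1, 12.8% for q = 0.8 and 21.6% for q = 0.6.

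**3. Chance of a significant harm finding with no true effect.** Approximately Φ(difference/SE − 1.96), with SE = √{[p1(1−p1) + p2(1−p2)]/n} and p1 now the apparent withdrawn risk.

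- At 881 per group: about 34% for f = 5% and 86% for f = 10%.
- At the pilot's 8,021 per group: about 47% for f = 2% and over 99% for f = 5%.

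Large databases shrink the standard error, not this bias.

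**4. Mortality in arm 3 with no true effect.** Assume background 5-year mortality of 3% or 5%, and that a share f of arm 3 stopped in a terminal or critical illness with 90% mortality. Arm 3 mortality = 0.9f + (1−f) × background.

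| f | Background 3% | Ratio | Background 5% | Ratio |
|---|---|---|---|---|
| 1% | 3.87% | 1.29 | 5.85% | 1.17 |
| 2% | 4.74% | 1.58 | 6.70% | 1.34 |
| 3% | 5.61% | 1.87 | 7.55% | 1.51 |

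Every input in step 4 is an assumption. Steps 2 to 4 give the planned weighting no credit, so they illustrate sensitivity and do not estimate the bias.

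**5. What the protocol implies about reasons for withdrawal.** The Introduction describes guidance changes in 2015–2018 that halved prescribing in women; those withdrawals fall inside the 2014–2024 window and are largely regulatory. It dates the UK restriction that extends to men from January 2024, while the study period ends on 01/01/2024. UK withdrawals in men within the window therefore mostly arose for other reasons, which are not stated. Men are 8,991 of 14,234 (63%) in the pilot and 29,332 of 44,647 (66%) in the CPRD feasibility count.

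**The case against.** **The covariate list is open.** The causal graph settles the final set, and the linked ED, inpatient and mortality data would allow recent admissions to be added. This stands in part. Added covariates do not change eligibility, and they do not decide whether a stay already open at time 0 is an outcome. If people who stop treatment while dying have few counterparts among continuers, weighting cannot balance them.

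**This is detail that a condensed article leaves to a fuller plan.** That is fair for exact look-back windows and lags. But the article does state eligibility, time 0 and a confounder list, and the point concerns what those stated rules admit.

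**Not every reduction qualifies.** This stands. Arms 1–3 require withdrawal, and arms 1 and 2 also require a new drug, so a temporary reduction during an illness does not fit them. A patient who dies during a taper may never be classed as withdrawn, which would lower early mortality in those arms. If time 0 is the discontinuation date after a long taper, the trigger may lie well before follow-up.

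**Selection may run the other way.** This stands. Withdrawal for regulatory reasons or in remission could make arms 1–3, and especially the arm with no new drug, healthier than arm 4. The 12-month seizure count would adjust for part of that.

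**Arm 4 can contain acutely ill patients too.** True, since its matched prescription is not restricted to routine care. The difficulty is that illness can cause entry to arms 1–3, whereas the arm 4 date is set by matching on time.

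A reader might go further and infer that early deaths and admissions in arms 1–3 are reverse-caused, or that the pilot difference is an artefact of this kind. The protocol supports neither. It gives no reasons for withdrawal and no share of withdrawals made in acute illness.

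**Conclusion.** The concern holds as a design weakness with a possible, unquantified bias. The stated rules let an illness that prompted the change in valproate also generate early outcomes in arms 1–3, and no listed covariate identifies such an illness. Some early deaths, admissions and seizure codes may therefore be reverse-caused, in the direction of Hypothesis 1.

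The size cannot be derived from the protocol. Under the assumed inputs, unadjusted, a 1–3% share of terminal or critical stopping gives mortality ratios of 1.17 to 1.87, and a 5% share of triggered withdrawals gives 3.5 points in ED attendance. Planned adjustment would remove some of this, and opposing selection could offset or reverse it. The net sign is not established. The change is still worth making because even a small share could produce significance at the planned scale.

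**What to change.** 1. **Covariates.** Put into the causal graph and the weighting model ED visits and admissions shortly before time 0 (for example 30 and 90 days), time since last seizure code, and palliative-care codes, beside the 12-month seizure count. The windows are a suggestion.
2. **One time-0 rule for all four arms.** Require that time 0 is not during a hospital stay and that there is no palliative-care code. Choose arm 4's matched prescription under the same rule.
3. **Outcomes.** Count only encounters that begin after time 0, so that an open stay is not an event.
4. **Sensitivity analyses.** (a) Leave out, in every arm, patients with an acute admission in the 30 days before time 0. (b) Drop the first weeks to months of follow-up in every arm. The second also removes any genuine early harm of withdrawal, so it should support the main analysis and not replace it.

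The two stated dates for time 0 must be reconciled first, because these rules depend on the date used.

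**Cost.** Changes to eligibility, covariate and outcome wording. The linked primary care, ED, inpatient and mortality data should supply most of the variables, and data access was still being sought at the time of writing. The price is a modest loss of withdrawn patients, and results that apply to withdrawal decided outside an acute illness. That is close to the planned-withdrawal question posed for Aim 2.

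### Seizure, depression and some fall outcomes depend on a care contact being coded, and contact after time 0 may differ between the withdrawal arms and arm 4 in a way that baseline weighting cannot remove

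*Protocol article*

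**What the plan says.** The section on target trial emulation using TriNetX and CPRD takes data "linked across primary care, ED, inpatients, outpatients, and mortality subsets" and adds: "All coded events will be recorded for flexible categorical or continuous analyses, as needed". The outcome list under Target trial design includes "Seizures (symptom codes);Falls;Injuries;Burns;Aspiration pneumonia;Manic/bipolar episodes;New-onset depression;Self-harm/suicide", together with deaths, ED/hospital admissions and a composite of seizures, injuries, admissions and depression. No arm has scheduled outcome assessment.

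Under Treatment assignment, time 0 is: "Baseline (time 0) will be defined as when valproate dose reduction commences (treatment arms 1–3) or prescription of valproate at a matched time (arm 4"). Under Start and end of follow-up, the same time 0 "will be defined as when valproate treatment discontinued (treatment arms 1–3"). The contrast is arms 1–3 against arm 4.

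The analysis uses a "time-to-first-event approach (Cox-proportional hazards model) for deaths, new-onset depression and composite morbidity". For the rest: "A recurrent events approach (e.g., Prentice-Williams-Peterson Total Time Model) would be taken for the remaining outcomes". Emulated randomisation rests on g-methods applied to baseline confounders. The final set is to be chosen with a causal diagram, for the purpose of controlling confounding.

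For Aim 2, the prediction model forces treatment arm in and predicts a composite that again contains seizures and depression.

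**The concern.** Three fixed features combine. The exposed outcomes are seen only through coded contacts. The index event is a treatment change in three arms and a matched prescription in the fourth. All adjustment is made at time 0.

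If a medication change is followed by more contacts, more of the same underlying seizures and low mood will be written down in arms 1–3. This is a measurement difference that arises after baseline. Balancing the arms at baseline does not touch it, and neither does adding a confounder. Even baseline contact rate as a covariate would miss contacts generated by the switch itself.

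The exposure varies by outcome. Seizure symptom codes and new-onset depression are the most exposed. Falls are exposed only in part, because injurious falls tend to reach acute care by themselves. Deaths and ED/hospital admissions are little exposed.

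Hypothesis 1 expects some outcomes to be worse after withdrawal. If recording is higher in arms 1–3, the artefact points the same way. It would also carry into the composite morbidity index and the arm-specific risks of the Aim 2 model. Under Pathways to impact, the Aim 1 figures and a link to that model are meant for a national decision support tool.

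**Working it through.** **1. The plan's own figure.** Table 1 uses p1 = 2977/8021 = 0.3712 and p2 = 2471/8021 = 0.3081. Then n = (1.960 + 0.842)² × (0.2334 + 0.2132) / 0.0631² = 881 per group. This reproduces and is not in dispute. It concerns ED attendance, which is not one of the exposed outcomes.

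**2. Inputs for the size of the artefact.** The document gives no contact rate for any arm, so these are assumptions: contact rate c of 2 or 3 a year in arm 4 and 3 or 4 a year in arms 1–3; an event is coded only if a contact falls within a recall window w of 0.25 or 0.5 year; there is no true effect.

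**3. Ratio while the contact difference lasts.** The capture probability is 1 − exp(−c·w).

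- w = 0.25: c = 2 gives 0.393; c = 3 gives 0.528; c = 4 gives 0.632.
- w = 0.5: c = 2 gives 0.632; c = 3 gives 0.777; c = 4 gives 0.865.

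The spurious rate ratio r is the capture in arms 1–3 divided by that in arm 4.

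**4. Ratio if the difference lasts one year.** With a constant event rate and complete follow-up of T years, the ratio over the whole period is 1 + (r − 1)/T.

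| Contacts/year, arm 4 vs arms 1–3 | w (years) | r while it lasts | Over 5 years | Over 10 years |
|---|---|---|---|---|
| 2 vs 3 | 0.25 | 1.34 | 1.07 | 1.03 |
| 2 vs 3 | 0.5 | 1.23 | 1.05 | 1.02 |
| 2 vs 4 | 0.25 | 1.61 | 1.12 | 1.06 |
| 2 vs 4 | 0.5 | 1.37 | 1.07 | 1.04 |
| 3 vs 4 | 0.25 | 1.20 | 1.04 | 1.02 |
| 3 vs 4 | 0.5 | 1.11 | 1.02 | 1.01 |

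Five years is the horizon under Target trial design, and ten is the one under Start and end of follow-up. The Abstract speaks of 1–10 years. Over a one-year horizon the undiluted column applies.

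**5. What a small ratio does in a large sample.** Take no true effect and an assumed recorded risk of 0.20 in arm 4. The chance of a significant result in the direction of harm is Φ((d − 1.96·se0)/se1), where d is the difference in recorded risk and se0 and se1 are its standard errors under the null and the alternative. With equal recording it is 2.5%.

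- 5% more recording (0.21 vs 0.20): 7.5% at 881 per group and 35% at the pilot's 8,021 per group.
- 10% more recording (0.22 vs 0.20): 18% and 88%.

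**6. Direction.** If follow-up starts when dose reduction commences, contacts during the taper fall after time 0 and add recorded outcomes in arms 1–3. If it starts at discontinuation, those contacts fall before time 0. They can then raise coded seizure frequency over the preceding 12 months, which is a listed adjustment variable. Arms 1–3 would look more severe at baseline than they are, and the adjusted contrast could move the other way.

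**The case against.** The strongest reply is that extra contact is nowhere stated. A reader might infer that time 0 triggers extra reviews only in arms 1–3, so that more recording will be read as harm. The document does not support that. It gives no review frequency for any arm, and arm 4's index is also a prescribing event. Arm 3 starts no new drug, so it need not be seen more in the long run than patients who keep collecting valproate. Extra contacts may also be caused by real seizures. This stands, and the point is limited to what may happen.

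Second, reviews around a medication change are likely to be transient, so the 1.11–1.61 range should not be carried over the whole follow-up. This also stands. Dilution is incomplete, however: results are planned from one year, censoring at treatment deviation shortens follow-up, and in a first-event analysis an early code ends follow-up.

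Third, the pilot's ED risk ratio of 1.20 (0.3712/0.3081) is no yardstick for home seizures or low mood. Agreed; it is not used as one here.

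Fourth, deaths and ED/hospital admissions are already separate outcomes and little exposed. That is a real strength, and the fix builds on it.

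Fifth, sensitivity analyses are often left to a fuller plan, which is not shown, and the causal diagram may add contact frequency. Their absence is therefore not counted as an error. What remains is that adjustment for baseline confounders, as fixed in the article, cannot reach a recording difference that arises after time 0.

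Finally, making acute-care events the main outcomes would change the question, above all for depression, where only severe cases would remain. That also stands, and the fix does not ask for it.

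**Conclusion.** The concern holds as a risk, not as a demonstrated bias. Seizure codes, new-onset depression and, in part, non-injurious falls are open to differential recording after an index date that means different things in arms 1–3 and arm 4. The planned weighting cannot remove it.

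The size rests wholly on assumed contact rates and recall windows: a spurious rate ratio of 1.11–1.61 while a contact difference lasts, falling to about 1.02–1.12 over 5 years and 1.01–1.06 over 10 if it lasts one year. The bias would be concentrated early, and in samples of the planned scale a modest ratio can reach significance. Apparent harm is the likely direction if follow-up starts at dose reduction. The direction is not settled until the two time 0 definitions are reconciled. The document does not support saying that the hypothesis will be confirmed by recording alone.

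The matter affects what may be concluded about Hypothesis 1 for these outcomes and about both composites. It can be dealt with cheaply before data are seen: under Study status and timeline, data permissions are still being sought.

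**What to change.** Keep the any-setting outcomes as planned and reconcile the two statements of time 0. Pre-specify alongside them:

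- A version of seizures, falls, injuries, depression and the composite restricted to events recorded at ED attendance, unplanned admission or death.
- At least one negative-control outcome that is coded at routine contacts and not plausibly affected by antiseizure medication, analysed with the same weights and models.
- Contact rates by arm over time, with results for the first year and for later follow-up shown separately.

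State in advance how these will be read. Base conclusions of harm for contact-dependent outcomes on agreement with the acute-setting version and with the deaths and ED/hospital admissions already planned. Judge the negative control by its estimate and interval against a pre-stated margin, not by significance alone, because at this sample size a trivial difference could be significant.

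The cost is a setting flag on data already to be linked, one extra outcome and some additional tables. The acute-setting version will have fewer events and describes only events that lead to acute care, which is why it sits beside the main version and does not replace it.
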